### Statistical analysis

First, a descriptive analysis will be conducted of the variables studied. For quantitative variables, measures of centralization and dispersion will be collected. For qualitative variables, a frequency analysis will be carried out.

To analyze cross-sectional and longitudinal differences, hypotheses will be contrasted at a 95% confidence level. To contrast differences between both groups (TG and CG) at baseline and post-treatment at a given time, Student’s *t*-test will be used (for strong violations of the normality assumption, the Mann-Whitney U-test) or analysis of variance (ANOVA). The effect size will be calculated using Cohen’s d.

To test whether the treatment produces differences over time (baseline, post-treatment, 3 months, 6 months and 12 months in the TG and baseline and post-treatment in the CG) in each of the groups, the *t*-test for related samples will be used (Wilcoxon signed-rank test in the event of strong violations of the normality assumption) or with an ANOVA for repeated variables and multiple regression model to control possible confounding variables (such as: age, gender, HbA1c, time with diabetes, etc.). For qualitative variables, McNemar’s test will be used.

To study the relationships between the different variables, Pearson’s correlation coefficient and linear regression models will be used for interval variables. The relationship between qualitative variables will be evaluated with the χ2 test.

Possible risk factors will be studied through logistic regression analysis (analysis of adherence to the treatment program).

The analyses will be carried out considering the subjects who complete the program. Analyses will also be carried out according to the protocol.

Analysis of the results will begin when the TG subjects have completed all of the phases of the treatment program. An improvement in the different variables will be taken into account in the following cases: significant differences in p≤0.05 and in the case of the BDI-FS when there is a decrease in the level of depressive symptomatology (moderate-mild, mild-minimum).

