## Material and methods

### Study design and participants

This study is a longitudinal randomized control-group pretest-posttest clinical trial (S1 Table). Patients with type 1 diabetes who present depression (mild to moderate) and meet the inclusion criteria will be randomized through a computer program to 2 groups. The treatment group (TG) will receive the 9-week Web-based treatment, while the control group (CG) will comprise patients on the waiting list. Evaluations in the TG will be conducted at the beginning of the program (baseline), at completion and during follow-up (3, 6, and 12 months) after treatment. For ethical reasons, the CG will receive the Web-based treatment once the TG intervention has been completed. The CG will thus be assessed at the beginning and at the end of the TG treatment. At this point, the CG will begin treatment, provided the participants still meet the eligibility criteria, and will have their corresponding evaluations. The assessments will be conducted in person.

The participants will be individuals with type 1 diabetes from the province of Malaga (Spain) who meet the following criteria:

○ Inclusion criteria: medical diagnosis of type 1 diabetes ≥ 1 year; over 18 years of age; psychological diagnosis of mild/moderate major depressive disorder, dysthymia or depressive symptomatology; no concomitant pharmacological treatment that could modify blood glucose values or depressive symptomatology; no psychological treatment at the present time; absence of the following: chronic renal failure, impaired liver function tests, active thyroid disease (except correctly substituted hypothyroidism), current pregnancy or acute ketosis decompensation at the beginning of the study; Internet access.○ Exclusion criteria: type 2 diabetes; women who are pregnant or planning to become pregnant; severe macrovascular or microvascular complications; diagnosis of major depressive disorder with risk of suicide; non-collaboration (no signed informed consent); presenting a disabling psychiatric disorder; psychosis; no Internet access.

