Clinical data and glycemic control will be collected through the medical record form of the visit to the physician and the data provided by the participant.

The primary variable is depression. Depressive symptoms during the previous 2 weeks will be assessed through a self-administered 7-item questionnaire (0–3), the BDI-FS [43]. For the diagnosis of depression, the Structured Clinical Interview for Major Depression Episode of the DSM-V will be used [44].

Among the secondary variables, fear of hypoglycemia will be evaluated with the Fear of Hypoglycemia questionnaire (FH-15) [45], which consists of 15 negative items on a Likert-type scale (1–5), and diabetes-related distress using the Spanish version [46] of the Diabetes Distress Questionnaire (DDS) by Polonsky et al., [47] which has 16 Likert-type items (1–5). The DDS provides a total distress score and 4 specific scores: affective distress; distress associated with the doctor-patient relationship; regimen-related distress and interpersonal distress. Quality of life will be assessed with the Diabetes Quality of Life Questionnaire [48], which evaluates quality of life specifically in individuals with diabetes mellitus. The Spanish version [49] has 43 questions (1–5) and 4 subscales: Dissatisfaction, Impact, Social/vocational concern and Concern for future aspects. Anxiety will be addressed using the Spanish version [50] of the State-Trait Anxiety Inventory (STAI) [51]. The STAI consists of 2 scales: State Anxiety (STAI-S) and Trait Anxiety (STAI-T). Each scale includes 20 self-administered items (0–3). Coping will be evaluated with the Spanish version [52] of the COPE inventory [53], composed of 5 scales assessing problem-centered coping, another 5 scales measuring emotion-centered coping, and 3 scales measuring less useful coping responses. Adherence to treatment will be evaluated with the 15-item (1–5) Spanish version of the Diabetes Self-Care Inventory-Revised questionnaire [54]. Personality will be evaluated using the Millon Clinical Multiaxial Inventory-III Spanish version [55]. This questionnaire contains 175 items with true or false answers. It consists of 11 basic personality scales, 3 pathological characteristics scales, 7 moderate syndrome scales and 3 severe syndrome scales.

The results of the trial will be published in peer-reviewed journals and presented in conferences.

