### Sample size calculation

We calculated the effect size using Cohen’s [56] estimates for the calculation of sample size a priori. For this, the significance level was considered to be 0.05 and the power 0.80. Concerning the effect size, according to a recent review by Uchendu and Blake [14] on CBT in adults with diabetes, there is a moderate effect size (-0.43) in depression. Therefore, in our study, a moderate effect size (0.50) will be used. With these data, a sample size of 28 participants is needed. Since the study has 2 groups, 28 participants will be included in each of the groups (56 participants in total).

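### The between-arm test of post-treatment BDI-FS is unadjusted although baseline BDI-FS is measured in both arms; adjusting for it would sharpen the estimate at almost no cost

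*Protocol article*

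**What the plan says.** In the protocol article, Results assessed names the primary variable ("The primary variable is depression") and measures symptoms with the BDI-FS, seven items scored 0 to 3. Study design and participants confirms that the control group also has both measurements: "The CG will thus be assessed at the beginning and at the end of the TG treatment".

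The between-arm method is in Statistical analysis. It begins "To contrast differences between both groups (TG and CG) at baseline and post-treatment at a given time" and names Student's t-test, the Mann-Whitney U-test for strong non-normality, or ANOVA, with Cohen's d as effect size. No covariate, change score or group-by-time term is attached to it.

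The next paragraph turns to change over time, "baseline and post-treatment in the CG) in each of the groups". The paired tests, the repeated-measures ANOVA and a "multiple regression model to control possible confounding variables (such as: age, gender, HbA1c, time with diabetes, etc" belong there.

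On planning values, Sample size calculation says "the significance level was considered to be 0.05 and the power 0.80" and "a moderate effect size (0.50) will be used", and arrives at 28 per group.

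**The concern.** The between-arm contrast after treatment is the one comparison that randomisation protects, and it carries the trial's main claim. As written, it uses only the post-treatment scores. The baseline score enters the between-arm analysis solely through a separate test at baseline, which changes nothing in the post-treatment estimate.

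If baseline and post-treatment scores are correlated, part of the spread in the post-treatment difference is explained by where the two arms happened to start. Leaving that part in widens the confidence interval and lowers power. In a trial of 56 people, precision is scarce and the information needed to recover some of it is already collected. Because the article states the method, this is a choice that can be improved and not a detail left to a fuller document.

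**Working it through.** **Inputs from the article.** 28 per arm, 1:1; planning effect d = 0.50, so SD = 1; significance level 0.05; the cited review's effect of 0.43 in absolute value; BDI-FS at baseline and post-treatment in both arms; entry at BDI-FS 4 to 12 on a scale whose maximum is 7 × 3 = 21.

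**Assumed.** Two-sided testing (the article says only "hypotheses will be contrasted at a 95% confidence level"); r from 0.2 to 0.7, since no value is given; equal SDs and a common slope in the two arms; all 56 analysed.

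**Step 1: the plan's own figure.** A two-sample comparison needs n per arm = 2(1.96 + 0.84)² / 0.50² = 2 × 7.849 / 0.25 = 62.8, that is 63 (64 with the t distribution). The stated 28 per group does not reproduce. That is a separate matter; 28 is used below because it is what the plan fixes.

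**Step 2: power of the planned test.** Noncentrality = 0.50 × √(28/2) = 1.871; the critical t on 54 df is 2.005; power = 0.45. At d = 0.43 it is 0.35.

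**Step 3: what chance imbalance contributes.** The baseline difference between arms has SD √(2/28) = 0.267 SD units. By the normal distribution, a gap above 0.25 SD has probability about 0.35 and one above 0.50 SD about 0.06. The unadjusted post-treatment difference has the same variance, 2/28 = 0.0714. Of that, a share r² comes from the baseline gap and a share 1 − r² from everything else. ANCOVA removes the first share.

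**Step 4: power with ANCOVA.** Noncentrality = [d / √(1 − r²)] × √14, on 56 − 3 = 53 df.

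| Assumed r | SD carried in from baseline gap (0.267 × r) | Reduction in SE | Power, d = 0.50 | Power, d = 0.43 |
|---|---|---|---|---|
| unadjusted | – | – | 0.45 | 0.35 |
| 0.2 | 0.05 | 2% | 0.47 | 0.36 |
| 0.3 | 0.08 | 5% | 0.49 | 0.38 |
| 0.5 | 0.13 | 13% | 0.56 | 0.45 |
| 0.7 | 0.19 | 29% | 0.73 | 0.60 |

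**Step 5: can adjustment rescue the sample size?** For 80% power with 28 per arm, 1 − r² must be at most 28 / 62.8 = 0.446, so r must be at least √0.554 = 0.74 by the normal approximation, and slightly more with the t distribution.

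**Step 6: is a change score equivalent?** No. Its variance is 2(1 − r) against 1 for the raw score, so it is worse whenever r is below 0.5. By the normal approximation, power at d = 0.50 is 0.35 at r = 0.3 and 0.46 at r = 0.5, against 0.46 for the raw comparison.

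**The case against.** The strongest reply is that nothing here is invalid. A randomised comparison of post-treatment means is unbiased over randomisation and holds its type I error. That is correct, and it limits the point to efficiency. A reader might infer that chance imbalance biases the result, or count it as a harm on top of lost precision. Neither follows: the imbalance averages zero and is already inside the unadjusted standard error, so there is one loss and not two.

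The second reply is that the gain may be small. This also stands. The article gives no r, and restricting entry to scores of 4 to 12 tends to weaken the correlation. At r of 0.2 to 0.3 the gain is about 1 to 4 percentage points of power.

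The third reply is that the regression sentence already adjusts. It does not reach this contrast, because it concerns change within each group. For the same reason, three stronger readings fail:

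- Baseline BDI-FS is not wrongly missing from the confounder list. In the over-time analysis it is already one of the repeated measurements, and the list is open-ended.
- Listing HbA1c, which is also an outcome, does not show that post-treatment HbA1c will be used for adjustment. The article does not say, and timing of covariates is detail that a condensed article may leave out.
- The baseline comparison between arms is a reporting preference. The article does not say that it will alter the effect estimate.

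Last, the change is not wholly free: the article's section on the intervention says that important protocol modifications are reported to the researchers, the university and the registry. That is a small administrative step.

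**Conclusion.** The point holds as one of precision. The article fixes an unadjusted between-arm test while holding a baseline measurement of the same variable in both arms. At 28 per arm and d = 0.50, baseline adjustment moves power from 0.45 to between 0.47 and 0.73 as r runs from 0.2 to 0.7, with the lower part of that range plausible given the entry window. The reading of the text is firm. The size of the benefit is uncertain because r is assumed, and the figures presume that all 56 participants are analysed.

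A reader might take this as a remedy for the trial's low power. It is not one: 28 per arm would still fall short of 80% unless r reached about 0.74 or more. The sample-size calculation has to be dealt with on its own.

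**What to change.** In Statistical analysis, make the primary between-arm test an ANCOVA of post-treatment BDI-FS on arm with baseline BDI-FS as covariate, and report the adjusted difference with its 95% CI. Use the same form for each continuous secondary outcome, with that outcome's own baseline value. Where normality is strongly violated, use a baseline-adjusted rank-based or robust version instead of the unadjusted Mann-Whitney test. Do not substitute a test on change scores.

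The cost is one degree of freedom and a change of wording, made before outcome data are analysed and reported as a protocol modification. No further data collection is needed.

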#### Procedure

The participants will be individuals with type 1 diabetes who regularly attend consultations in the Clinical Management Unit of Endocrinology and Nutrition of 2 hospitals (tertiary care) and a specialty center (secondary care) of the Andalusian Health Service of the province of Malaga (Spain) who voluntarily choose to participate in the study. The participants will not receive any type of economic or material remuneration.

Patients will be recruited through information posters placed in the visible areas of the Units, inviting them to participate in the study, either directly by sending an e-mail or through their physician. Those interested in participating will be evaluated by a psychologist from the research group who will assess the inclusion and exclusion criteria. Depressive symptoms will be evaluated with the Beck Depression Inventory-FastScreen (BDI-FS) [43] Patients with a BDI-FS score greater than or equal to 4 and less than 13 who meet the rest of the inclusion criteria and none of the exclusion criteria will sign the informed consent. All questions about the study will be answered, and the necessary aspects clarified, ensuring that the participant has understood everything he or she has read. The participants will then be prepared to begin the study and the initial assessment will be conducted.

Once the sample has been randomized, the participants will be notified of the group to which they have been assigned by e-mail. Those assigned to the CG will be given encouragement while they wait to begin treatment after the TG has completed the treatment (Fig 1).

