## Conclusions

In this article, we present the design and methodology of the WEB_TDDI1 study, which includes a specific proposal for the treatment of mild-moderate depressive symptoms in adults with type 1 diabetes delivered through a Web-based CBT program. Based on previous studies, we anticipate an improvement in depressive symptomatology with respect to the control group and to baseline status, as well as an improvement in the secondary variables studied related to depression (anxiety, diabetes-related distress, fear of hypoglycemia, coping strategies, quality of life and adherence to diabetes treatment). Thus, this program is expected to provide professionals with a tool to treat mild to moderate depressive symptomatology in people with type 1 diabetes. Additionally, an analysis of the characteristics related to adherence to this program will be carried out to help establish profiles of people who will benefit from this type of treatment.

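### A valid between-arm test is planned, but the treatment question and the improvement rule rest on within-arm change, which also carries regression to the mean and natural recovery

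*Protocol article*

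**What the plan says.** The Statistical analysis section of the protocol article contains two families of tests and one rule for calling a result an improvement.

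- **Between arms.** The first contrast is introduced with "To contrast differences between both groups (TG and CG) at baseline and post-treatment at a given time". It uses Student's t-test, Mann-Whitney or ANOVA, with Cohen's d as effect size.
- **Within arms.** The question about the effect of treatment comes next: "To test whether the treatment produces differences over time (baseline, post-treatment, 3 months, 6 months and 12 months in the TG". The tests named are the paired t-test, Wilcoxon signed-rank, repeated-measures ANOVA with a regression model for confounders, and McNemar for qualitative variables. No group-by-time term is stated, and the part of the sentence on the control arm confirms that each arm is tested separately: "baseline and post-treatment in the CG) in each of the groups".
- **Improvement rule.** The general criterion reads "An improvement in the different variables will be taken into account in the following cases: significant differences in p≤0.05". A second criterion, a change of severity category, is attached for the primary scale: "in the case of the BDI-FS when there is a decrease in the level of depressive symptomatology (moderate-mild, mild-minimum".

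Two design facts matter. Entry is on the outcome scale itself (Procedure): "Patients with a BDI-FS score greater than or equal to 4 and less than 13". The control group has no untreated assessment after the end of the treatment group's programme (Study design and participants): "The CG will thus be assessed at the beginning and at the end of the TG treatment". The Conclusions section expects both kinds of result: "we anticipate an improvement in depressive symptomatology with respect to the control group and to baseline status".

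**The concern.** A test inside one arm shows whether scores changed, not whether the programme changed them. The participants were chosen because their BDI-FS was raised, and such scores tend to fall back when measured again. Mild and moderate depressive symptoms also remit on their own. Randomisation separates these influences from the treatment effect, but only in a comparison of the arms.

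The article does plan that comparison, but it does not say that it decides efficacy. The sentence that speaks of what the treatment produces points to the within-arm tests, and the improvement rule can be met without reference to the control group. A report that follows this wording could credit the programme with a change that the waiting list shows too, or could read a significant fall in the treatment group beside a non-significant one in the control group as evidence of effect. At 3, 6 and 12 months there is no untreated comparator, so a causal reading of those tests has no support at all.

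**Working it through.** **Inputs from the protocol article.** Entry at BDI-FS 4 to 12 (Procedure); 28 participants per arm (Sample size calculation); significance at 0.05; scale range 0 to 21 (7 items scored 0 to 3). The article states no error rate for the within-arm tests, so there is no figure to reproduce.

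**Assumed inputs, because the article does not give them.** Source-population mean 2.5 to 6 and SD 3 to 3.5; correlation r between occasions 0.6 to 0.8; levels cut at 4, 9 and 13. Only 4 and 13 appear in the article, as entry bounds; the mild/moderate cut at 9 is an assumption. No treatment effect and no natural recovery are built in.

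**Why scores fall.** Let S be the screening score, B a later baseline score, Y the post-treatment score and m the population mean. With no true change and roughly normal scores:

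- If S is the baseline: E(Y − S | S) = −(1 − r)(S − m). For illustration, with S = 6, m = 2.5 and r = 0.6, this is −0.4 × 3.5 = −1.4 points.
- If BDI-FS is measured again: E(Y − B | S) = −(r_SB − r_SY)(S − m). With equal correlations this is zero, because the regression has already happened before baseline. If correlation weakens with time (r_SY < r_SB), part of the fall returns.
- Between arms: the expected value of Y given entry is the same in both arms, so the expected difference is zero in either case.

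**Simulation, screening score as baseline** (28 per arm, 8,000 trials per scenario):

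| Assumed mean / SD, r | Mean fall | Drop a level | Paired test in treatment group declares improvement |
|---|---|---|---|
| 2.5 / 3, 0.6 | 1.2 | 42% | about 72% |
| 4 / 3.5, 0.7 | 0.71 | 31% | 29% |
| 6 / 3.5, 0.8 | 0.2 | 21% | about 8% |

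The nominal rate in the direction of improvement is 2.5%. The treatment group is significant while the control group is not in 7 to 25% of trials.

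**Simulation, BDI-FS measured again at baseline, equal correlations.** Mean fall 0.00; paired test declares improvement in 2 to 3% of trials; 16 to 24% of participants still drop a level (21% in the middle scenario). By symmetry as many rise a level, so a count of falls alone credits pure measurement noise.

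**Between-arm t-test at t2.** About 5% two-sided rejection in both cases, as intended.

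**The case against.** The strongest reply is that the valid test is already there. The between-arm contrast is the first inferential test listed, it carries an effect size, and the Conclusions name the control group before baseline status. This stands. A reader might infer that the plan compares no arms or throws away randomisation; the text does not support that. What is missing is a statement that this contrast takes precedence.

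Second, the large error rates depend on using the screening score as baseline. The Procedure describes an initial assessment after screening and consent, the caption of Fig 1 separates the eligibility screen from the t1 baseline, and Table 2 lists BDI-FS at baseline. A fresh measurement is at least as natural a reading, and under equal correlations it brings the paired test back to its nominal rate. This stands too, so the 8 to 72% cannot be quoted as the plan's error rate without that condition. It does not rescue the level-drop criterion, and natural recovery would still count as improvement under either reading.

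Third, the improvement rule may mean significance plus a clinically relevant shift, and it does not say whether the level is judged per person or per group. That is fair, but on either reading no difference from the control group is required, and a decrease in level most naturally means a decrease from an earlier level.

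Three further inferences should be resisted. That a fall from 8 to 4 would not count needs a mild/moderate cut-off that the article never gives. The unlisted step from moderate to minimum is probably shorthand. The absence of a control group at 3 to 12 months is a disclosed feature of the waiting-list design, adopted for ethical reasons; those data can describe maintenance, and only a causal reading is at fault.

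Finally, modelling detail may sit in a plan that is not shown. But the article itself fixes which tests answer the treatment question and what counts as improvement, and an analysis plan that followed it would inherit the problem.

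**Conclusion.** The concern holds as a fault of precedence and wording, and should be fixed. The between-arm post-treatment test is sound and stays at about 5% with no effect. The within-arm tests and the improvement rule, as worded, can credit regression to the mean or natural recovery to the programme.

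The size depends on a point the article leaves open. If the screening score is the baseline, the within-arm paired test declares improvement in about 8 to 72% of trials with no true change, and 21 to 42% of participants drop a level. If BDI-FS is measured again at t1 with equal correlation between occasions, the test is nominal (2 to 3%) but 16 to 24% still drop a level. All these figures rest on the assumed means, SDs and correlations and on the cut at 9. Natural recovery is left out and would add to them.

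**What to change.** Change the Statistical analysis wording as follows.

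1. State that efficacy is decided by the between-arm difference in BDI-FS at t2, adjusted for baseline BDI-FS. The unadjusted t-test is already valid; adjustment adds precision and uses data already scheduled.
2. Compare the proportions with a level drop, and with a SCID diagnosis, between arms at t2 (logistic regression or Fisher's exact test) instead of by McNemar within arm.
3. Reword the improvement rule so that it requires the between-arm difference.
4. Label within-arm tests, and the treatment group's results at 3, 6 and 12 months, as descriptive of course and maintenance, with no efficacy claim.
5. Say whether baseline BDI-FS is the screening score or a new measurement at t1.

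No further data are needed, since both arms are assessed at baseline and t2. The cost is that pre-post and follow-up claims become weaker and the conclusion rests on the between-arm test. Its power with 28 per arm and the article's effect size of 0.50 is Φ(0.5 × √(28/2) − 1.96) = Φ(−0.09) = 0.46 unadjusted. With baseline adjustment the first term is divided by √(1 − ρ²), giving 0.50, 0.58 or 0.75 for an assumed pre-post correlation ρ of 0.3, 0.5 or 0.7. The sample size is a separate matter, but within-arm tests should not be used to make up for it.
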